### Plans to promote participant retention and complete follow-up {18b}

Laboratory tests at the follow-up visit are all necessary to observe condition alterations or to ensure the safety of the patient. The current study showed that nucleic acid conversion was delayed compared to viral culture and was highest at 14 days, so we collected nucleic acid samples again at day 14 [22].

### Data management {19}

This project is adopting electronic data management, and the relevant information of patients will be recorded in the electronic medical record system and entered onto the eCRF. Data management will be carried out through an electronic data capture system.

### Confidentiality {27}

All datasets will be stored on the research platform of the Clinical Information Management Suite and password-protected. The principal investigators have direct access to all datasets through this research platform. To ensure confidentiality, data distributed to project team members will be kept confidential from any information identifying participants.

### Plans for collection, laboratory evaluation, and storage of biological specimens for genetic or molecular analysis in this trial/future use {33}

It is not applicable. All collected specimens will be used to evaluate condition alteration and safety of intervention and will not be used for other studies. We did not collect and use of participant data and biological specimens in the current trial, and for future use, additional consent provisions are not necessary for our protocol.

## Statistical methods

### Statistical methods for primary and secondary outcomes {20a}

All data will be analysed using SAS software, version 9.4 (SAS Institute Inc., USA). A two-tailed *p* < 0.05 will be considered statistically significant in all statistical tests (except for the main efficacy indicators and other specified instructions).

The full analysis set (FAS), modified intention-to-treat set (mITT), per-protocol set (PPS), and safety set (SS) will be divided for analysis. FAS includes all eligible and randomized patients. PPS includes eligible patients with better compliance (80–120%), and completing necessary items of CRF.SS includes all patients enrolled in the study who have received at least one dose of medication and have at least one safety evaluation. Baseline characteristics analysis will be based on FAS, efficacy analysis will be based on FAS and PPS, and safety analysis will be based on SS. Unblinded patients will be excluded from PPS.

Continuous data will be summarized as the mean ± standard deviation, median, minimum, maximum, lower quartile, and upper quartile. Categorical data will be presented and summarized as frequencies and percentages in each category.

Between-group comparisons will be conducted by using paired *t*-tests or Wilcoxon rank tests for continuous data, chi-square tests or Fisher exact tests for categorical data, Wilcoxon rank tests or CMH tests for ranked data, and Kaplan‒Meier estimates for time-to-event data. The principles of intention-to-treat analysis will be used.

Efficacy analysis will be based on FAS and PPS. The primary efficacy endpoints are COVID-19-related critical illness and all-cause mortality within 28 days (whichever happens first), which will be analysed based on a time-to-event manner. Kaplan‒Meier method will be used to describe the incidence rates of the primary endpoint in each group separately at 28 days. Between-group comparisons will be performed by the log rank test. A Cox regression model will be used to estimate the hazard ratio and corresponding 95% confidence interval and adjust for potential covariates such as centres. Secondary efficacy endpoint analysis will be performed according to general statistical considerations. The specifics of these methods will be thoroughly outlined in the statistical analysis plan.

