### Criteria for discontinuing or modifying allocated interventions {11b}

#### Participants will withdraw from the study for any of the following reasons:

Participants with poor compliance who cannot cooperate with the clinical examination and follow-up.Patients who voluntarily quit this clinical trial.

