### Sample size {14}

This study aims to determine the efficacy of a new antiviral compared to placebo in reducing critical illness or all-cause mortality on day 28 in COVID-19 patients.

The sample size was calculated based on the superiority test. The primary endpoints are the disease critical rate and mortality rate. Based on the data reported in Hong Kong for patients with COVID-19 from the end of 2020 to March 2022, the number of deaths and serious illnesses was 6866 and 8875, respectively [21]. Previous data on another antiviral drug, Paxlovid, showed that the placebo group had 65 hospitalizations and 12 deaths, while the Paxlovid group had no deaths and 8 hospitalizations [5]. Combined with data from Hong Kong, it was speculated that there may be 15–16 severe patients in the placebo group and 2 severe patients in the Paxlovid group. Therefore, the disease critical rate and mortality rate in other countries and China are assumed to be 2.6% in the standard treatment group and can be reduced to 0.19% with effective treatment. With a power of 90% (1 sided *α* = 0.025 and *β* = 0.10), a sample size of 986 patients in each group is needed. The sample size calculations were performed using SAS software, version 9.4 (SAS Institute Inc., USA).

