### Procedure for unblinding if needed {17b}

The Interactive Response Technology (IRT) system will be programmed with instructions to maintain blinding. For anticipated and unanticipated serious adverse events, emergency unblinding may be performed only if the investigator must know the treatment grouping information to proceed in the event of an emergency in the subject (e.g. requiring resuscitation). The safety of the participant will always be the primary consideration in making this decision. The reason for unblinding and the date it occurs must be documented in the source documentation and case report form (CRF). The study-specific IRT reference manual and investigational product manual will provide contact information and further details on how to use the IRT system.

Unless efficacy is demonstrated at an interim analysis, the study will be unblinded after the statisticians finalize the statistical plan and the audit report in the data plan and lock the database. Details of the unblinded sponsor staff supporting the independent data monitoring committee (IDMC) and the timing of unblinding will be outlined in the unblinding plan.

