### Interim analyses {21b}

An interim analysis is planned to assess both efficacy and futility, and a sample size re-estimation will be conducted once the 548th participants in the mITT analysis set complete the day 28 assessments. The IDMC, supported by an unblinded statistical centre, will regularly review safety data and evaluate the interim efficacy analysis.

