### Methods in analysis to handle protocol nonadherence and any statistical methods to handle missing data {20c}

The primary endpoint is defined as time-to-event data, non-endpoint events will be defined as censoring events, and the censoring date will be set as the last follow-up date. No carry-forward or multiple imputations will be conducted for missing data.

Missing data of secondary endpoints or safety endpoints will not be imputed. Missing data due to intercurrent events will be imputed by a multiple imputation approach under a prespecified estimand.

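### The unranked per-protocol efficacy set excludes patients for events close to the primary endpoint, the multiple-imputation sentences conflict, and censoring of withdrawn patients may be informative

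*Protocol article*

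**What the plan says.** All references are to the protocol article.

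- **Analysis sets (section 20a).** Efficacy is to be analysed on FAS and PPS, with no statement of which leads. Intention-to-treat principles are said to apply, and "FAS includes all eligible and randomized patients". PPS requires 80–120% compliance and completed case report form items, and "Unblinded patients will be excluded from PPS". The primary endpoint is time to first critical illness or death within 28 days, compared by log-rank test.
- **Unblinding (section 17b).** Individual "emergency unblinding may be performed only if the investigator must know the treatment grouping information to proceed in the event of an emergency"; the example given is resuscitation.
- **Withdrawal (section 11b).** Patients leave the study if they quit voluntarily or fall under "Participants with poor compliance who cannot cooperate with the clinical examination and follow-up". A separate list in the same section covers stopping medication, including on worsening illness.
- **Missing data (section 20c).** Patients without a primary event are censored at last follow-up, and "No carry-forward or multiple imputations will be conducted for missing data". Secondary and safety data are not to be imputed. The next sentence says "Missing data due to intercurrent events will be imputed by a multiple imputation approach under a prespecified estimand".

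**The concern.** The primary endpoint is mechanical ventilation, ECMO, high-level oxygen support or death. An emergency that justifies breaking the blind will often be that endpoint or lie close to it. Removing such patients from PPS selects that set on something near the outcome. The compliance limit can do the same when an event interrupts dosing. This would be tolerable in a set declared supportive, but the article gives PPS the same standing as FAS and makes no exception for exclusions caused by the event.

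The missing-data text leaves no endpoint to which the multiple-imputation instruction can apply without contradicting another sentence. An analyst cannot follow all the sentences at once.

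Withdrawal from the study, unlike stopping the drug, ends observation. If patients who stop cooperating have a different risk from those who stay, censoring them at last contact biases FAS as well. Few events are expected, so a handful of unseen ones could matter.

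**Working it through.** **1. Reproduce the design figure.** Inputs from section 14: rates "assumed to be 2.6% in the standard treatment group and can be reduced to 0.19% with effective treatment", one-sided α = 0.025, power 90%. With unpooled variance:

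n per arm = (1.960 + 1.282)² × [0.026 × 0.974 + 0.0019 × 0.9981] / (0.026 − 0.0019)²
= 10.508 × 0.02722 / 0.000581 ≈ 492.4, rounded up to 493.

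Two arms need 986. Dividing by 0.9 gives 1,096, or 548 per arm, which matches section 15. (Section 14 words 986 as a per-group number; the arithmetic shows that it is the two-arm total. That is a separate point.)

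**2. Expected events and dropouts.**
- Placebo: 548 × 0.026 = 14.2. Azvudine: 548 × 0.0019 = 1.0. Total: 548 × 0.0279 = 15.3.
- If only the 493 per arm left after dropout are counted: 493 × 0.0279 = 13.8.
- Planned dropout: 1,096 − 986 = 110, about 55 per arm.

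**3. Compliance limit.** Dosing is once daily for 7 days (section 11a). The article does not give the denominator for compliance. If it is the planned 7 days, dosing that ends after day 5 gives 5/7 = 71%, below 80%, and after day 6 gives 6/7 = 86%, which passes. On that assumption an event that stops dosing by day 5 takes the patient out of PPS. If the denominator is doses due up to the event, it does not.

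**4. Unblinding.** The permitted trigger in section 17b is an emergency in the patient. The PPS exclusion in section 20a covers every unblinded patient, with no distinction between unblinding before the endpoint event and at or after it. This route does not depend on the compliance denominator.

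**5. Imputation rules side by side (section 20c).**

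| Endpoint | Rule stated | Room for multiple imputation |
|---|---|---|
| Primary | Censor at last follow-up; no multiple imputation | None |
| Secondary | Not imputed | None |
| Safety | Not imputed | None |
| Missing because of intercurrent events, endpoint not named | Multiple imputation required | Conflicts with each row above |

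**6. How sensitive is the planned test?** With equal arms and rare events, the log-rank statistic is approximately z = (a − b)/√(a + b), where a and b are the placebo and azvudine event counts. At 493 per arm the design split is about 13 v 1.
- 13 v 1: z = 12/√14 = 3.21, one-sided p about 0.0007.
- 7 v 1 (six placebo events lost from PPS): z = 6/√8 = 2.12, p about 0.017, still below 0.025.
- 13 v 5 (four unseen azvudine events added): z = 8/√18 = 1.89, p about 0.03, just above 0.025.

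The last case needs 4 events in about 55 azvudine dropouts, or 7.3%. That is 2.8 times the assumed placebo rate of 2.6%, with no unseen event in placebo dropouts. At the placebo rate, 55 × 0.026 = 1.4 would be expected.

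**The case against.** Several parts of the case against are right and limit the point.

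- **FAS keeps these patients.** Under-dosed and unblinded patients stay in FAS, and intention-to-treat principles are stated. Excluding them from a per-protocol set is common practice. This stands: the selection affects PPS only. What remains is that PPS is not ranked below FAS and has no exception for event-driven exclusions.
- **The withdrawal rule.** A reader might infer that it drops patients because of the primary event. The text does not say so. It names poor compliers who cannot cooperate with follow-up and voluntary quitters; worsening illness appears only in the list for stopping medication. Section 18a also plans daily monitoring in hospital and a day-28 survival call. Informative censoring is a possibility here, not something that the rule builds in.
- **Eligibility in FAS.** A reader might infer that randomised patients later judged ineligible are removed. Section 16a randomises eligible patients, and no later removal is described. The definition is loose, not demonstrably wrong.
- **The imputation sentences.** They can be read as a general rule with an exception for intercurrent events. The mention of a prespecified estimand, and a statistical plan finalised before final unblinding (section 17b), count against any inference that the method will be picked after seeing results. But the article does not mark the sentence as an exception or name its endpoint, so the conflict stands.
- **The interim trigger.** A reader might object that it counts patients "once the 548th participants in the mITT analysis set complete the day 28 assessments", a set that section 20a gives no analysis. A trigger count biases no estimate, so this is not part of the point.
- **Fragility.** A reader might infer that losing a few events overturns the result. At the full design effect and under the planned log-rank test, losing six placebo events from PPS does not.

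**Conclusion.** The point holds in a limited form, and the text should be changed.

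- The PPS efficacy result is conditioned on events close to the primary endpoint. The unblinding exclusion does this as written; the compliance limit does so only if compliance is measured against the planned 7 days. FAS is untouched by either.
- The imputation sentences in section 20c conflict and must be reconciled.
- Censoring of withdrawn patients may be informative in FAS. The planned number of dropouts (about 110) is roughly seven times the expected number of events (110/15.3 = 7.2), so the matter deserves a sensitivity analysis. At the design effect, only an extreme pattern of unseen events moves the log-rank p-value past 0.025.

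The event counts rest on the design rates of 2.6% and 0.19%, and the dropout count on the planned 10%. The size and direction of any bias cannot be derived from the document.

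**What to change.** 1. Define FAS as all randomised patients and name it the primary efficacy set.
2. Declare PPS supportive. Count compliance over doses due up to the endpoint event, and do not exclude a patient for unblinding at or after that event.
3. Keep one rule for the primary endpoint: censor at the last date known to be event-free, and at day 28 at the latest. Delete the multiple-imputation sentence, or state which endpoint and which intercurrent events it covers and amend the sentence that it overrides.
4. After withdrawal for poor compliance, keep collecting day-28 critical illness and vital status unless consent is withdrawn.
5. Add one tipping-point sensitivity analysis of the primary endpoint for dropouts.

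The cost is wording in the protocol and analysis plan plus slight extra analysis work. Telephone contact at day 28 is already scheduled (sections 13 and 18a). As section 18a describes that call as collecting survival status, a question on critical illness would need to be added.

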### Trial design {8}

This is a prospective multicentre, placebo-controlled, randomized, double-blind phase III trial, with a superiority design. A total of 1096 symptomatic adult patients with COVID-19 infection who are at increased risk of progressing to critical illness, based on their demographics and comorbidities, will be recruited from January 2023 through January 2024 [5]. The patients will be randomized at a 1:1 ratio to the treatment group and placebo group and treated with azvudine and placebo, respectively (Additional file 1). The investigator will observe and record subjects’ disease progression or remission and adverse drug reactions and analyse the data. Double blinding will be used in the trial.

This protocol was designed according to the Standard Protocol Items: Recommendations for Interventional Trials (SPIRIT) 2013 Statement (Additional file 2) [18] and registered at ClinicalTrials.gov (ID: NCT05689034).

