### Recruitment {15}

To account for a 10% dropout rate, the sample size increased to 1096 participants (548 in the azvudine group and 548 in the control group). To enrol enough participants, we set up special screening staffs in the fever clinic and emergency department where COVID-19 patients often visit, and screening staffs distribute COVID-19 antigen to suspected fever patients to identify candidates. In order to complete such large amount patients’ selection as soon as possible, we selected 46 study sites localized in 17 different provinces in China Mainland; thus, we will obtain timely enrolment to the greatest extent possible.

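### Paired t-tests are named for comparing two unmatched randomised arms; secondarily, the ordinary Cox hazard ratio has no finite estimate whenever the azvudine arm has no event

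*Protocol article*

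**What the plan says.** **Continuous outcomes.** Section {20a} of the protocol article states: "Between-group comparisons will be conducted by using paired" t-tests or Wilcoxon rank tests for continuous data. It does not say whether the Wilcoxon test is the rank-sum or the signed-rank form. The same section analyses secondary efficacy endpoints under its general statistical rules, so this sentence governs the continuous secondary outcomes listed in section {12}: viral load at days 1, 3, 7 and 14, and days in hospital and intensive care.

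**Design.** Section {8} states: "The patients will be randomized at a 1:1 ratio to the treatment group and placebo group". Section {16a} describes permuted-block randomisation. Neither mentions matching.

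**Primary endpoint.** Section {20a} names Kaplan-Meier rates at day 28, the log-rank test, and a Cox model that gives a hazard ratio with a 95% confidence interval and is to "adjust for potential covariates such as centres". It leaves the specifics to the statistical analysis plan, which is not shown. Section {15} says that "we selected 46 study sites localized in 17 different provinces", and section {14} takes the event rates as "assumed to be 2.6% in the standard treatment group and can be reduced to 0.19% with effective treatment".

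**The concern.** A paired t-test analyses differences within pairs. Two independently randomised arms supply none, so the analyst would have to invent a pairing, and with unequal arm sizes the test cannot be run at all. Reading the phrase as a before-after test does not help, because that tests change within one arm and not the treatment contrast. This is a test stated wrongly, not a detail left open, and an analysis plan that follows the article would inherit the error.

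The Cox point is different in kind. The model is a normal choice, but the rates used to size the trial imply about one primary event in the azvudine arm. If that arm has none, the partial likelihood keeps rising as the hazard ratio goes to 0, so there is no finite estimate and no usable Wald interval. The intended effect measure would then be missing when the drug works as well as assumed.

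**Working it through.** **1. The paired test.** No arithmetic applies. Section {20a} names a paired test between groups, while sections {8} and {16a} describe parallel, unmatched arms. The two cannot be reconciled.

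**2. The plan's own sample size.** Inputs from section {14}: "assumed to be 2.6% in the standard treatment group and can be reduced to 0.19% with effective treatment" and "With a power of 90% (1 sided *α* = 0.025 and *β* = 0.10". With the unpooled-variance formula:

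n per arm = (1.960 + 1.282)² × (0.026 × 0.974 + 0.0019 × 0.9981) / (0.026 − 0.0019)² = 492.4, so 493 per arm and 986 in total.

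Allowing for 10% dropout: 986 / 0.9 = 1096 in total, and 493 / 0.9 = 548 per arm. This matches section {15}: "To account for a 10% dropout rate, the sample size increased to 1096 participants (548 in the azvudine group". Section {14} writes "a sample size of 986 patients in each group is needed", but 986 reproduces only as the total of both arms. That is a separate inconsistency. The calculations below use 548 per arm (everyone followed) and 493 per arm (after 10% dropout).

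**3. Expected primary events.**

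| | 548 per arm | 493 per arm |
|---|---|---|
| Azvudine, 0.19% | 1.04 | 0.94 |
| Control, 2.6% | 14.2 | 12.8 |
| Total | 15.3 | 13.8 |

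**4. Chance of no azvudine event**, (1 − p)^n:

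| Azvudine rate p | n = 548 | n = 493 |
|---|---|---|
| 0.19% (plan) | 0.9981^548 = 35.3% | 0.9981^493 = 39.2% |
| 0.3% | 19% | 23% |
| 0.5% | 6% | 8% |
| 1.0% | under 1% | under 1% |

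Simulation of 20,000 trials gave 35.2% and 38.7% at the plan's rate. At the interim look (548 participants in all, about 274 per arm) the figure is 0.9981^274 = 59.4%. If 986 per arm were taken literally it would be 0.9981^986 = 15.3%. A control arm with no event has probability below 0.00001.

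**5. Is centre adjustment the cause?** In 400 simulated trials at 548 per arm, analysed by centre-stratified Cox models, 34.0% had no azvudine event and 33.8% of fits diverged. None of the 264 trials with at least one azvudine event diverged. The empty arm is the cause, and an unadjusted model fails equally often.

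**6. Centres.** Fifteen events can fall in at most 15 of 46 sites, so at least 46 − 15 = 31 sites have none. With equal-sized sites (assumption) about 33 to 34 have none. Such sites add nothing to a stratified treatment estimate, and as separate terms their coefficients would have no finite value.

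**7. Day-1 adjustment for viral load.** Relative to an unadjusted comparison, the variance is multiplied by 1 − r². The documents give no correlation r. For an assumed r of 0.4 to 0.6 the factor is 0.84 to 0.64, a reduction of 16% to 36%.

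**The case against.** On the paired test, the best defence is that the word is a slip and that the same sentence also offers Wilcoxon rank tests. A paired analysis of unmatched arms would probably be noticed before it produced a p-value. That limits the harm but does not make the text right, and the Wilcoxon wording is itself unspecific. Adjusting for day-1 viral load is an efficiency choice. An unadjusted two-sample comparison is valid, so its absence is not an error.

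On the Cox model, the objection carries more weight. The article gives centres only as an example of a potential covariate. It prescribes neither 46 terms nor a Wald interval, and it defers the specifics to the analysis plan, which may already contain a rule for an arm without events. Even then a profile-likelihood interval is informative: with 0 against 14 events and near-equal risk sets, 28 × ln(1 + HR) = 3.84 gives an upper limit of about 0.15.

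Three stronger readings are tempting, and the documents support none of them:

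- **Centre adjustment makes the hazard ratio fail in over a third of trials.** The failure comes from the empty azvudine arm and would remain with every centre term removed.
- **The primary result could not be reported.** The log-rank test and the day-28 Kaplan-Meier rates are already planned and remain computable with no events in one arm.
- **The paired test would distort p-values by a known amount.** Any such figure would reflect an arbitrary pairing that nobody planned.

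**Conclusion.** The paired t-test is wrong as written and should be corrected. This rests only on the article's own description of the design and needs no assumption. It affects the continuous secondary outcomes and not the primary test.

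The Cox point is a worthwhile, inexpensive improvement rather than an error. On the plan's rate of 0.19% and its planned size, the ordinary hazard ratio has no finite estimate in 35% to 39% of trials. This depends strongly on that optimistic rate: it is 19-23% at 0.3% and under 1% at 1.0%. It also assumes that the analysis plan does not already provide a remedy.

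**What to change.** 1. In section {20a}, replace the paired t-test with the two-sample t-test, and name the Wilcoxon test as the rank-sum test.
2. For viral load, use ANCOVA or a repeated-measures model on log viral load, adjusted for the day-1 value. State that the day-1 swab precedes the first dose, which the article does not say. No new data are needed, and the precision gained depends on the actual correlation.
3. Keep the log-rank test as the primary test. Pre-specify a Firth-penalised Cox hazard ratio with a profile-likelihood interval, and report the day-28 Kaplan-Meier risk difference with its interval. The method for that interval must remain valid when one arm has no events.
4. Avoid separate terms for 46 centres with about 15 expected events; at most, stratify by pooled region.

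The cost is wording in the protocol and analysis plan. The methods are available in the named software. The one statistical price is that the penalised hazard ratio is shrunk slightly towards 1.
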